# PREPARE: protocol for a stepped wedge trial to evaluate whether a risk stratification model can reduce preterm deliveries among women with suspected or confirmed preterm pre-eclampsia

**DOI:** 10.1186/s12884-019-2445-x

**Published:** 2019-10-07

**Keywords:** Pre-eclampsia, Preterm birth, Prematurity, sFlt-1/PlGF, fullPIERS

## Abstract

**Background:**

Preeclampsia (PE) is a major cause of short and long-term morbidity for affected infants, including consequences of fetal growth restriction and iatrogenic prematurity. In Brazil, this is a special problem as PE accounts for 18% of preterm births (PTB). In the PREPARE (Prematurity REduction by Pre-eclampsia cARE) study, we will test a novel system of integrated care based on risk stratification and knowledge transfer, to safely reduce PTB.

**Methods:**

This is a stepped wedge cluster randomised trial that will include women with suspected or confirmed PE between 20 + 0 and 36 + 6 gestational weeks. All pregnant women presenting with these findings at seven tertiary centres in geographically dispersed sites, throughout Brazil, will be considered eligible and evaluated in terms of risk stratification at admission. At randomly allocated time points, sites will transition to risk stratification performed according to sFlt-1/PlGF (Roche Diagnostics) measurement and fullPIERS score with both results will be revealed to care providers. The healthcare providers of women stratified as low risk for adverse outcomes (sFlt-1/PlGF ≤38 AND fullPIERS< 10% risk) will receive the recommendation to defer delivery. sFlt-1/PlGF will be repeated once and fullPIERS score twice a week. Rates of prematurity due to preeclampsia before and after the intervention will be compared. Additionally, providers will receive an active program of knowledge transfer about WHO recommendations for preeclampsia, including recommendations regarding antenatal corticosteroids for foetal benefits, antihypertensive therapy and magnesium sulphate for seizure prophylaxis. This study will have 90% power to detect a reduction in PTB associated with PE from a population estimate of 1.5 to 1.0%, representing a 33% risk reduction, and 80% power to detect a reduction from 2.0 to 1.5% (25% risk reduction). The necessary number of patients recruited to achieve these results is 750. Adverse events, serious adverse events, both anticipated and unanticipated will be recorded.

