## Methods/design

This is a stepped wedge cluster randomised trial for the implementation of an intervention at hospital level to evaluate whether a risk stratification model can reduce the incidence of preterm deliveries among women with suspected or confirmed preeclampsia. The trial will be conducted in seven tertiary centres, geographically dispersed throughout Brazil, and will run for 48 months; with data collection for 32 months. The participating tertiary centres and respective cities are: Fernandes Figueira Institute, Rio de Janeiro; Maternity Maria Amélia Buarque de Holanda, Rio de Janeiro (these two hospitals constitute one centre for the study); Maternity Leila Diniz, Rio de Janeiro; Botucatu Medical School, Botucatu-SP; Center for Women’s Health – CAISM, Campinas-SP; Hospital Guilherme Álvaro, Santos-SP; Maternity Leonor Mendes de Barros, São Paulo; Hospital of Clinics of Porto Alegre-RS.

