### Statistical issues

#### Sample size

The primary aim is to test whether care targeted at preventing unnecessary delivery of women with pre-eclampsia will reduce the proportion of women delivered in the centres with preterm pre-eclampsia (deliveries with preterm pre-eclampsia/total deliveries). The power calculation depends on estimates of the total number of births, current pre-eclampsia prevalence and proportion with preterm deliveries from the seven centres (which have already agreed to participate). We estimate the mean number of infants born in each month per centre to be 330, and that of these ~ 5% will be born to women with pre-eclampsia. The preterm rate among those women with pre-eclampsia is approximately 36%. Therefore each month, there will be the potential to enter 17 women with pre-eclampsia, of whom approximately 6 would deliver prematurely, and outcome data will be available for approximately 700 deliveries of women with preterm pre-eclampsia. There is limited information on likely intracluster correlation (ICC) for this outcome in this setting and so we have explored sensitivity to a range of values.

Power calculations for stepped wedge cluster trials were as described in Hussy and Hughs [18]. Assuming that seven centres take part and allowing for a one month transition phase, and that in each centre there are approximately 17 cases of pre-eclampsia and 330 deliveries per month (with outcome data available for all deliveries), this study will have 89.6% power to detect a reduction in preterm deliveries associated with pre-eclampsia in the study centres from a population estimate of 1.5 to 1.0%, representing a 33% risk reduction, and 79.6% power to detect a reduction from 2.0 to 1.5% (25% risk reduction). Although the ICC is included in the power calculation, the design was found to be insensitive to the ICC and sensitivity analyses showed that these calculations were robust to larger magnitudes of ICCs.

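### The 750 recruited patients called necessary for the power, and the roughly 700 preterm pre-eclampsia deliveries, do not follow from the plan's own inputs; the stated power rests on about 71,600 deliveries over 32 months

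*Protocol article*

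**What the plan says.** The abstract (Methods) states 90% power for a fall from 1.5 to 1.0% and 80% power for a fall from 2.0 to 1.5%, followed by "The necessary number of patients recruited to achieve these results is 750". That number appears nowhere else in the article and has no derivation.

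The Sample size section derives the same powers (89.6% and 79.6%) from other quantities. It begins "Assuming that seven centres take part and allowing for a one month transition phase" and continues that "in each centre there are approximately 17 cases of pre-eclampsia and 330 deliveries per month (with outcome data available for all deliveries" (the bracket closes there). On the expected case load it says that each month "there will be the potential to enter 17 women with pre-eclampsia, of whom approximately 6 would deliver prematurely". The same sentence then says that "outcome data will be available for approximately 700 deliveries of women with preterm pre-eclampsia".

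Methods/design says the trial "will run for 48 months; with data collection for 32 months". The primary outcome divides deliveries with preterm pre-eclampsia by total deliveries. The Data analysis section leaves out outcomes from the transition months.

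**The concern.** The abstract ties the power to a count of recruited patients, while the Sample size section ties it to delivery volume. The primary outcome has all deliveries as its denominator, so a count of recruited women cannot by itself be the size that produces the power. The count of 700 also sits in the same sentence as a rate that, multiplied out over the planned centres and months, gives almost twice as many.

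The stake is how the number gets used. Sites, ethics committees, the monitoring committee and later readers may take a figure described as necessary to be the target, and judge progress or completion against it. In a stepped wedge, stopping on a count would cut off the centres that cross over last.

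**Working it through.** **Inputs.** From Sample size: 7 centres; 330 deliveries and 17 pre-eclampsia cases per centre-month; about 5% of births to women with pre-eclampsia; 36% of these preterm; about 6 preterm cases per centre-month; one transition month per centre. From Methods/design: 32 months of data. From Randomisation, recruitment and collection of baseline data: one centre crosses every four months after a four-month baseline, so 4 + 7 x 4 = 32 months, which agrees. Assumed because the article does not give them: two-sided alpha 0.05, and an intracluster correlation (ICC) of 0.001 to 0.1.

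**Step 1. Analysable size.** 7 x 32 = 224 centre-months, less 7 transition months = 217.
- Control: 4 + 8 + ... + 28 = 112 centre-months, x 330 = 36,960 deliveries.
- Intervention: 27 + 23 + ... + 3 = 105 centre-months, x 330 = 34,650 deliveries.
- Total: 217 x 330 = 71,610 deliveries.

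**Step 2. Reproduce the stated power.** Stepped-wedge power by the method the article cites: fixed monthly period effects, random centre effect, transition months dropped, binomial variance p(1-p) at the mean of the two rates, power = Φ(|p1 - p2|/SE - 1.96).

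| Scenario | Stated | ICC 0.001 | ICC 0.01 | ICC 0.1 |
|---|---|---|---|---|
| 1.5 to 1.0% | 89.6% | 93.0% | 91.5% | 91.3% |
| 2.0 to 1.5% | 79.6% | 83.0% | 80.6% | 80.3% |

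For ICC 0.01 and above, the recomputed powers are within 2 points of the stated ones and hardly move with the ICC, as the article says. The power therefore comes from all deliveries over 32 months.

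**Step 3. Counts of women that the inputs give.**

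| Quantity | Calculation | Result |
|---|---|---|
| Women with pre-eclampsia | 17 x 7 x 32 | 3,808 |
| Preterm pre-eclampsia deliveries, 6 per centre-month | 6 x 7 x 32 | 1,344 |
| Same, without transition months | 6 x 217 | 1,302 |
| Same, at 5% x 36% = 1.8% | 71,610 x 0.018 | 1,289 |
| Events, 1.5 to 1.0% | 36,960 x 0.015 + 34,650 x 0.010 | 901 |
| Events, 2.0 to 1.5% | 36,960 x 0.020 + 34,650 x 0.015 | 1,259 |

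None of these is 700 or 750. Spread over 71,610 deliveries, 700 events is 0.98%, below even the lowest rate in either power scenario.

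**Step 4. What if 750 were used as a target?** At 6 x 7 = 42 preterm cases a month, 750 is reached after 750/42 = 17.9 months. At month 18, four of the seven centres have entered transition. The Step 2 model cut at month 18 gives 63-70% (1.5 to 1.0%) and 49-56% (2.0 to 1.5%) for ICC 0.001 to 0.1. At a 1.5% rate the monthly count is 0.015 x 330 x 7 = 34.65, so 750 would come no earlier than month 21.6. The month-18 figures are an illustration.

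**The case against.** The strongest reply is that nothing in the design depends on 750. The Sample size section never uses it, the duration is fixed by calendar, and the rollout ends with four months in which all centres are exposed. A stop at month 18 would mean abandoning that rollout. This stands. A reader might infer that the trial is underpowered, but the document does not support that: with the calendar followed, the stated powers hold.

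Three further points also stand.
- A reader might say that 700 and 750 contradict each other. They are in different units, deliveries with outcome data and recruited patients, so the gap between them is not itself an error.
- A reader might compute the power with only 700 to 750 events over all 32 months and find a large loss in the second scenario. That calculation lowers the event rates (for 750 events, to about 1.19 and 0.89%), so it is not a test of the 2.0 to 1.5% effect that the plan states.
- The size in deliveries is only unprinted, since its factors are all given.

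The counts may also have a legitimate origin. Half the data period gives 6 x 7 x 16 = 672, and 1.0% of 71,610 is 716. The article says neither, so this suggests a meaning without supplying one. What the reply does not remove is a plain statement that 750 patients are necessary for power that was calculated from something else.

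**Conclusion.** The point holds as an error in the stated sample size, not as a failure of power. At the stated monthly rates, 750 is about one fifth of the women with pre-eclampsia (750/3,808) and a little over half of the preterm cases (750/1,344). The 700 is also about half of what the rate in its own sentence gives (700/1,344). The 89.6% and 79.6% are approximately right for about 71,600 deliveries over 32 months. The arithmetic on counts uses only the article's figures; the power check also rests on the assumed two-sided 0.05 and ICC range. The loss of power in Step 4 is conditional on 750 being treated as a recruitment target, which the document does not say.

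**What to change.** - In the abstract, remove 750 as the number necessary for the power, or define what it counts (unit, phase and rate) and separate it from the power statement.
- In Sample size, correct the 700 or define it in the same way.
- State the size as about 71,600 analysable deliveries (217 centre-months x 330). Give the expected events: about 900 under 1.5 to 1.0%, about 1,260 under 2.0 to 1.5%, and about 1,290 at the plan's own 1.8% rate.
- Say explicitly that the 32-month calendar, not a count of women, sets the end of data collection.

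The cost is a change of text in the abstract and the Sample size section. Design, schedule, analysis and number of patients stay as planned.

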**Discussion:**

The PREPARE intervention expects to reduce PTB and improve care of women with PE without significant adverse side effects. If successful, this novel pathway of care is designed for rapid translation to healthcare throughout Brazil and may be transferrable to other low and middle income countries.

**Trial registration:**

ClinicalTrials.gov: NCT03073317.

**Electronic supplementary material:**

The online version of this article (10.1186/s12884-019-2445-x) contains supplementary material, which is available to authorized users.

## Background

Pre-eclampsia (PE) is a serious, placentally-mediated disorder that affects about 5% of pregnant women worldwide and represents a major cause of maternal and perinatal mortality [1, 2]. Additionally, the impact of PE on the immediate and long-term health of the infant cannot be overestimated. Apart from perinatal death, preeclampsia is associated with preterm birth (PTB) and fetal growth restriction, with important sequelae of chronic neurological disability and adult cardiometabolic diseases [3–5]. Although several of the pathophysiological features of PE (e.g. reduced placental perfusion, increased inflammation, oxidative and endoplasmic reticulum stress etc.) can contribute to these adverse outcomes, iatrogenic preterm birth persists as a major factor in many countries.

In Brazil, PE causes 23% of all maternal deaths. Once PE has been diagnosed, measures such as antihypertensive therapy and magnesium sulphate may reduce maternal morbidity (such as eclampsia or stroke), but the only ‘cure’ for PE is delivery, regardless of gestational age. For this reason, PE is the indication for almost 18% of all preterm births and nearly half of all iatrogenic premature deliveries [6–9]. In high-income countries (HIC), indicated deliveries for PE are an important contribution to PTB, but account for about 8% [4]. It is possible that many women with mild or equivocal diagnosis of PE may also be delivered inappropriately early in Brazil, often by Caesarean section, owing to imperfect diagnostic and risk stratification methods leading to hasty and unnecessary intervention.

It is evident that the decision for immediate or delayed delivery in women with preterm PE is complex. While immediate delivery serves the interests of the mother, delayed delivery enhances maturation of the fetus and improves neonatal survival rates [10]. [name], one of the co-authors for this work, first developed methods in the United Kingdom more than 30 years ago for the expectant management of PE [11]. Considering the high rates of PTB related to PE in Brazil, a strategic approach for these cases becomes crucial. Therefore, this project aims to test whether the systemic application of an evidence-based risk stratification model can reduce preterm births among women with preterm PE in the country.

Two methods of risk stratification will be used to help obstetricians to make decisions regarding the best timing for delivery for women with suspected or diagnosed preterm PE. This application extends a recent Latin American trial of conservative management of very preterm PE, which did not have access to these objective risk stratifiers [12]. The first component of the PREPARE study intervention is the fullPIERS risk stratification algorithm. The fullPIERS algorithm is based on maternal symptoms, signs, and laboratory tests to accurately identify women at increased risk for maternal complications related to PE [13]. It predicts adverse maternal outcomes (AUROC 0.88) within 48 h but also performs well for up to the next seven days. Therefore, the fullPIERS model is able to identify those pregnant women who do not need immediate delivery, but do need continuing close surveillance. The second method uses the biomarker sFlt-1/PlGF ratio as a prognostic indicator for clinical need for delivery [14, 15]. In a prospective, multicentre, observational study, Zeisler et al. used a cohort of 500 women with suspected PE at less than 37 weeks to determine that sFlt-1/PlGF ratio cut-off of 38 had predictive value to indicate time to delivery. In this cohort, the negative predictive value of developing PE within one week was 98.9% with sensitivity of 88.2% and specificity of 80% [14]. In a validation cohort of additional 550 women, a cut-off of sFlt-1/PlGF ratio of 38 or lower had a negative predictive value of 99.3% for the development of PE within one week, sensitivity of 80% and specificity of 78.3%. Either fullPIERS or sFlt-1/PlGF strategies have more than 98% negative predictive value for adverse outcomes.

We will perform both of these determinations on women presenting with suspected or diagnosed PE in which hospital admission or delivery would usually be considered with conventional Brazilian practice. The fullPIERS assessment will be repeated twice weekly and sFlt-1/PlGF ratio weekly. For women with PE who are low risk by both assessments, we will recommend to care providers that delivery be delayed safely. Since greater than 95% of deliveries in Brazil occur in the hospital setting, this intervention is likely to have a high impact on reducing the number of unnecessary, iatrogenic preterm deliveries related to PE.

Changing the behaviour of care providers presents substantial challenges [16–22]. This is especially difficult in a setting in which we are changing what is likely perceived as a “less risky” to “more risky” approach with respect to maternal health. To address this challenge, a program of Knowledge Transfer (KT) will be introduced to all healthcare professionals involved with the management of pre-eclamptic patients in the participating centres [23, 24]. This program has been developed and tested by the Canadian Institutes of Health Research [25]. This KT will include information specifically relevant to the intervention. Thus it will include information about the excess of preterm births for precclampsia in Brazil, the hazards of preterm birth, the data upon which the intervention is based and the safety meausure instituted to assure the safety of the intervention.

In addtion, the PREPARE KT model will be based on the World Health Organization (WHO) recommendations for pre-eclampsia/eclampsia management, including the use of low-dose aspirin and calcium supplementation for prevention of pre-eclampsia. Evidence from meta-analyses indicates that calcium supplementation reduces the risk of pre-eclampsia by half (and even more in high-risk women). The benefit of aspirin is more modest with a 17% reduction in the risk of pre-eclampsia (25% in high-risk women) [3]. In Brazil calcium supplementation is given to less than 10% of women in whom it is indicated [26]. A recent work demonstrated high prevalence of inadequate calcium in two cohorts of pregnant women evaluated in Brazil [27].

Educational modules specific to the application and use of fullPIERS and sFlt/PlGF in the context of the trial will also be provided prior to implementation of the risk assessment strategy at each participating centre.

The PREPARE study will be implemented following a stepped wedge design. Clusters (in this case tertiary hospitals with maternity units) are identified to take part in a one-way cross-over cluster RCT and, before the trial begins, randomly allocated a start date from when they are given the intervention. The time they receive the intervention is randomly ordered [28]. The clusters crossover at regular intervals (in this case, every four months), from their current standard of care to the intervention program. The randomisation sequence is decided before the start of the trial, and is made known to each centre shortly before implementation.

This methodology is essential for this study because it would be challenging for one hospital to manage critical patients using two protocols concurrently, or to abandon the new, better methods when they have been introduced. Once the intervention has been introduced, it becomes part of the routine care for women with known or suspected preeclampsia in the hospital. Consent is carried out as for other routine hospital procedures.

The initial training in the new KT will be carried out by a skilled and experienced team moving from hospital to hospital. Also there will be a link to access e-modules for training that will be available for all professionals in the centres.

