### Aims and hypotheses

The aims of the PREPARE study are:
To test the hypothesis that risk stratification of women with suspected or confirmed pre-eclampsia based upon objective criteria reduces the proportion of medically-indicated preterm deliveries and improves neonatal outcomeTo evaluate whether use of and adherence to a Knowledge Transfer system will help to reduce preterm births in preeclampsiaCollect samples and individual patient data to establish a database and biological sample bank to search for unique risks and pathophysiological features. This will facilitate future studies and allow direct comparisons of demographic, metabolic and genetic factors in Brazil, other LMIC (Low and medium-income countries) and in HIC

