### Outcome measures

#### Primary

Proportion of women delivered in the centres with preterm pre-eclampsia (deliveries with preterm pre-eclampsia/ total deliveries), where preterm is < 37 weeks’ gestation.

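### The first two aims claim separate effects of risk stratification and of knowledge transfer, but the design estimates only the combined package, through a primary outcome that also falls if pre-eclampsia becomes less frequent

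*Protocol article*

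**What the plan says.** - **Aims.** Under Aims and hypotheses, the first aim is that "risk stratification of women with suspected or confirmed pre-eclampsia based upon objective criteria reduces the proportion of medically-indicated preterm deliveries". A second, separate aim is to evaluate whether using and adhering to a KT system helps to reduce preterm births in pre-eclampsia.
- **Package.** The Abstract describes integrated care that combines stratification with KT. The Intervention and Knowledge transfer program sections give every centre both, plus monthly monitoring of use and corrective seminars where use is deficient.
- **KT content.** The Background bases KT on WHO recommendations, "including the use of low-dose aspirin and calcium supplementation for prevention of pre-eclampsia". It adds that "calcium supplementation reduces the risk of pre-eclampsia by half", that "The benefit of aspirin is more modest with a 17% reduction in the risk of pre-eclampsia", and that "In Brazil calcium supplementation is given to less than 10% of women in whom it is indicated". The audience is "all healthcare professionals involved with the management of pre-eclamptic patients in the participating centres".
- **Primary outcome.** It is "deliveries with preterm pre-eclampsia/ total deliveries), where preterm is < 37 weeks’ gestation".
- **Secondary outcomes.** The first listed is the preterm share among pre-eclampsia deliveries.
- **Analysis.** The Data analysis section has a mixed model with centre, calendar time and one intervention-exposure indicator per centre and time point. Numbers of women developing pre-eclampsia are listed among the baseline characteristics, to be compared between exposure and non-exposure by summary statistics.

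**The concern.** There are two separate problems.

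**Attribution between components.** Each of the two aims names one component as the cause. A stepped wedge with a single exposure variable contrasts centre-periods that have everything with centre-periods that have, by intention, nothing. A positive result would say that the package works. It would not say whether the tests or the teaching did the work. The tests are a distinct part of the pathway that the Discussion proposes to offer to health authorities, so the difference matters to whoever must decide on adoption.

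**Attribution between mechanisms.** The Data analysis section describes a pathway aimed at preventing unnecessary delivery. That acts on when women with pre-eclampsia deliver. The primary outcome has all deliveries as its denominator, so it also responds to how many women have pre-eclampsia. If KT includes prevention, part of any fall could occur with no delivery deferred.

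**Working it through.** **1. What the design contrasts.** Seven centres cross over one at a time and end with stratification, KT and monitoring. No stratification-only or KT-only step is defined, and the model has one exposure term. The separate effects are therefore not identifiable from the randomised comparison. KT itself argues against early delivery (Knowledge transfer program, Phases 1 and 2), so both components push the timing of delivery in the same direction.

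**2. What the primary outcome is made of.** For any centre-period:

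preterm pre-eclampsia deliveries / all deliveries = (pre-eclampsia deliveries / all deliveries) × (preterm share among pre-eclampsia deliveries).

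Inputs from Sample size: 330 deliveries per centre-month, about 5% with pre-eclampsia, about 36% of those preterm.
- 330 × 0.05 = 16.5 (the protocol says 17)
- 16.5 × 0.36 = 5.94 (the protocol says about 6)
- 0.05 × 0.36 = 1.8%, between the two baseline rates used for power, 1.5% and 2.0%

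Prevention lowers the first factor. Deferral lowers the second.

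**3. The protocol's power figures.** Stated: 89.6% for 1.5% to 1.0%, and 79.6% for 2.0% to 1.5%. Check: Hussey-Hughes variance, 7 centres, 8 four-month periods (32 months), 4 × 330 = 1,320 deliveries per cell, 990 in each crossover cell after dropping the transition month, and binomial variance at the baseline rate. Two-sided 5% is assumed. The protocol gives no intracluster correlation (ICC). An ICC of 0.0005 gives 90.05% and 80.4%; 0.001 gives 88.4% and 78.3%. Both pairs are within 2 points of the stated figures, so the model serves for step 4.

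**4. How large the incidence route would have to be.** Take the protocol's halving of risk with calcium and a starting coverage of 10%. If coverage among women who would otherwise develop pre-eclampsia rises to c, and timing of delivery does not change, the relative incidence is

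RR = (1 − 0.5c) / (1 − 0.5 × 0.10) = (1 − 0.5c) / 0.95.

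The document gives no value for c, so the range is an assumption. The last two columns are the chance of a significant primary result from this route alone, at ICC 0.0005.

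| Coverage reached | RR | Fall in primary outcome | Baseline 1.5% | Baseline 2.0% |
|---|---|---|---|---|
| 20% | 0.947 | 5.3% | 7% | 9% |
| 30% | 0.895 | 10.5% | 17% | 22% |
| 50% | 0.789 | 21.1% | 54% | 66% |
| 70% | 0.684 | 31.6% | 87% | 95% |

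At ICC 0.001 the 50% row becomes 51% and 64%. To reproduce a whole design effect:
- RR 0.75: c = (1 − 0.75 × 0.95) / 0.5 = 57.5%
- RR 2/3: c = (1 − 0.667 × 0.95) / 0.5 = 73.3%

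**5. What the existing secondary outcome shows.** If incidence alone fell, and fell proportionally for preterm and term cases, the preterm share would stay at 36%. If timing alone produced the 33% reduction, it would fall to 36% × 2/3 = 24%. It therefore helps to tell the mechanisms apart. It does not tell stratification from KT.

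**6. When KT starts.** The legend to Fig. 1 places intensive KT in the four months before implementation, followed by the transition month. The Knowledge transfer program section makes the e-learning available at the transition. The Background puts modules on the tests before implementation at each centre. Data analysis counts a centre as exposed from one month after it is randomised to the intervention and drops only the transition months. On the Fig. 1 reading, KT falls in months counted as unexposed. Unexposed centre-months number 4 × (1 + 2 + … + 7) = 112. Four KT months in each of seven centres make 28, which is 28 / 112 = 25% of them, if KT fills all four months.

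**The case against.** **The prevention route rests on one Background statement.** Calcium and aspirin do not appear in the operational KT programme, and the treatments named in the Abstract and Intervention sections are corticosteroids, antihypertensives and magnesium sulphate. The audience manages women who are already affected, and no section describes giving either agent to women before disease. This stands. A reader might infer that a positive result would probably come from prevention; the documents do not support that. The coverage figures are assumptions, the coverage below 10% refers only to women in whom calcium is indicated, the formula assumes full effect from the first exposed month, and small uptake hardly moves the result.

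**The mechanism can be examined.** The preterm share and prolongation of pregnancy are secondary outcomes, and pre-eclampsia counts are compared by exposure. This largely stands. A reader might infer that the trial has no means of telling prevention from deferral, and that is too strong. What remains is that the incidence comparison is descriptive and is not stated to adjust for calendar time. In a stepped wedge, exposed months are later on average, so a secular trend would mix with the effect.

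**The protocol already describes a package.** The Abstract, Data analysis and Discussion speak of integrated care or a care pathway, and the Discussion offers the pathway, not the tests alone. Bundling is a normal pragmatic choice. This stands, and it supports rewording the aims, which still name the components one by one.

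**The second aim has its own data**, because use of the knowledge is graded monthly. True, but that comparison is not randomised.

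**All components do not clearly start at the crossover.** Correct, since the sections disagree. This does not rescue the second aim: no analysis uses the months before implementation as a KT contrast.

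**Conclusion.** The point holds in two parts of unequal strength.

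**Firm:** the primary analysis estimates the effect of the combined package. The component claims in the first two aims cannot be drawn from it. This follows from the design alone and does not depend on calcium, aspirin or any assumed uptake.

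**Qualified:** the primary outcome responds to pre-eclampsia incidence as well as to timing of delivery, and the Background gives KT a route to incidence. The size of that route is unknown and may be small. Under the stated assumptions it contributes little at 20% coverage and matches the design effects only at 57.5% or 73.3%. The preterm-share outcome can help to separate the routes, provided that incidence is analysed as carefully as the other outcomes.

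The trial remains a valid test of the package. What needs correction is what it says it can conclude. The disagreement on KT timing is a related defect: on the Fig. 1 reading, up to a quarter of the unexposed centre-months already contain KT.

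**What to change.** 1. Restate the first two aims so that the trial tests the combined package of stratification, KT and monitoring, in line with the Abstract and Data analysis. Label any analysis of KT use and adherence as non-randomised.
2. Move pre-eclampsia deliveries / total deliveries from the baseline characteristics to a named secondary outcome, analysed with the same time-adjusted stepped-wedge model. Define it over the same set of pre-eclampsia deliveries as the preterm-share outcome, so that the two multiply to the primary outcome.
3. State that a conclusion that the package works by deferring delivery requires the preterm share among pre-eclampsia deliveries to fall, and that even this does not isolate risk stratification from KT.
4. Reconcile the Background, the Fig. 1 legend and the Knowledge transfer program section on when KT starts, and make the exposure coding in Data analysis agree with the result.

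The cost is rewording, one extra model on counts already to be collected, and a narrower claim for the risk stratification tests.
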